#### Tertiary

The tertiary objectives are to evaluate the following epidemiological features in children diagnosed with mild CAP in the current era of universal vaccination with the 13-valent pneumococcal vaccine (PCV13) and include:To investigate various baseline characteristics in a cohort of children meeting study criteria for CAP, including the distribution of saliva C-reactive protein (CRP) values, the prevalence of *Streptococcus pneumoniae* high-level colonization (>10 000 genome copies/mL), in nasopharyngeal swab (NPS) specimens, how frequently *Mycoplasma pneumoniae* is detected in NPS samples, and what proportion of study participants with alveolar consolidation documented on chest radiograph have NPS specimens positive for at least one virus.To investigate whether these baseline characteristics differ substantially when stratified by age group (6–59 months vs. 5–10 years of age).To explore whether any of these baseline characteristics appear to be more common in children who do not achieve early clinical cure.

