#### Subgroup

We will also explore whether there are differential treatment effects of the 5-day course vs. the 10-day course on the primary outcome of cure in the following subgroups: (1) older (age 5–10 years) vs. younger (age <5 years); (2) higher vs. lower salivary CRP; and (3) virus/*mycoplasma* detected in baseline NPS vs. no virus detected.

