#### Analysis

We will use descriptive statistics to describe the baseline characteristics of the groups reported as count (percent) for categorical variables, and mean (standard deviation) or median (first quartile, third quartile) for continuous variables, depending on the distribution. We will adopt Consolidated Standards of Reporting Trials (CONSORT) criteria for reporting on non-inferiority and equivalence trials in reporting the trial [38]. The principal analysis will be per- protocol, as is recommended for non-inferiority trials [39–41]. The principal analysis is not intention-to-treat (ITT) simply because the effect of ITT analysis is to reduce the difference seen between treatment groups; in a superiority trial, ITT analysis functions to buttress a conclusion of superiority, but in a non-inferiority trial it could lead to a false conclusion of non-inferiority by masking a true difference between treatment arms.

We will use logistic regression to analyze binary outcomes, Poisson regression for count outcomes and linear regression for continuous outcomes. Descriptive analyses will be used to compare rates of viral and atypical co-infections in the entire study population and between groups.

We will perform some subgroup analyses by adding an interaction term between treatment group (5-day vs. 10-day course) and the following subgroups: (1) older (age 5–10 years) vs. younger (age <5 years); (2) higher vs. lower salivary CRP; and (3) virus/*Mycoplasma* detected in baseline NPS vs. no virus detected. These interaction tests will be exploratory in nature and not adjusted for multiple testing [42].

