Adherence to study medications	Better in short-course arm than in long-course arm	Daily symptom diaries, RA interview: “adherence” defined as > 80% amoxicillin doses given (<3 doses of initial 15 doses in short-course arm, < 6 doses in reference arm) Dichotomous	Logistic regression
Recurrence of respiratory illness after primary outcome visit but before 30-day follow up	Short-course treatment is non-inferior to long-course treatment	RA interview. Dichotomous	Logistic regression
Development of antibiotic-resistant organism (ARO) colonization	Less frequent in short-course arm than in long-course arm	Enteric swab testing: “new colonization”’ defined as 3–6 month swab ARO positivity in context of baseline swab ARO negativity. Dichotomous	Logistic regression
Disruption of gut microbiome	Less marked in short-course arm than in long-course arm	Enteric swab testing: comparison of gut microbiome at 3–6 months to baseline gut microbiome. Continuous	Linear regression
Tertiary, entire-cohort			
Distribution of salivary C-reactive protein in cohort	Mean will be greater than that observed in children with bronchiolitis but less than that observed in children with empyema	Salivary swab testing: continuous	Descriptive statistics expressed as mean (95% CI)
Prevalence of high-level *S. pneumoniae* nasopharyngeal colonization	Majority of cohort will be positive	Nasopharnygeal swab (NPS) testing: Dichotomous	Percentage, with 95% CI
Prevalence of *Mycoplasma* detection	Minority of cohort will be positive	NPS testing: Dichotomous	Percentage, with 95% CI
Subgroup analyses			
Older (age 5–10 years) vs. younger (age <5 years)	Older age group will have higher salivary CRP values, lower rates of *S. pneumoniae* high-level colonization, more *Mycoplasma* positivity, and decreased rates of clinical cure	Clinical cure (as defined above)	Logistic regression with an interaction term between subgroup and treatment variables
Higher vs. lower salivary CRP	Higher salivary CRP will be associated with decreased rates of clinical cure	Clinical cure	Logistic regression with an interaction term between subgroup and treatment variables
Virus/*Mycoplasma* detected in baseline NPS vs. no virus detected (for primary outcome)	Detection of a virus or *Mycoplasma* will not affect observed rates of clinical cure	Clinical cure	Logistic regression with an interaction term between subgroup and treatment variables
Sensitivity analyses – for primary outcome only			

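### Table 1 pairs three subgroup hypotheses about the factor's own effect on cure with a treatment-by-subgroup interaction test, which does not test them

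*Protocol article*

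**What the plan says.** Table 1 of the Protocol article (Statistical analysis, Analysis) sets a hypothesis and a method side by side for each outcome. Under Subgroup analyses:

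- Age: the hypothesis begins "Older age group will have higher salivary CRP values, lower rates of" and ends by predicting lower cure in the older group. It also predicts differences in CRP, pneumococcal colonization and Mycoplasma, although the only outcome in the row is clinical cure.
- CRP: "Higher salivary CRP will be associated with decreased rates of clinical cure".
- Virus/Mycoplasma: detection "will not affect observed rates of clinical cure".

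None of the three mentions treatment arm. The method is the same in each row: "Logistic regression with an interaction term between subgroup and treatment variables". The Analysis text agrees: "We will perform some subgroup analyses by adding an interaction term between treatment group (5-day vs. 10-day course) and the following subgroups". It adds: "These interaction tests will be exploratory in nature and not adjusted for multiple testing".

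Elsewhere the article asks two different questions.

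- Effect modification: the Subgroup objective says "We will also explore whether there are differential treatment effects of the 5-day course vs. the 10-day course on the primary outcome of cure". The secondary research question at the end of the Background also asks about covariates that modify the effectiveness of the short course.
- Prognosis: the third Tertiary objective is "To explore whether any of these baseline characteristics appear to be more common in children who do not achieve early clinical cure". The last item under Secondary outcomes asks whether cure rates are affected by baseline CRP, high-level pneumococcal colonization, Mycoplasma or virus.

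**The concern.** An interaction test asks whether the 5-day versus 10-day odds ratio differs between subgroups. The hypotheses beside it ask whether cure differs between subgroups. A factor can lower cure sharply and equally in both arms; the hypothesis is then true and so is the null of the test.

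Two misreadings become possible. In the age and CRP rows, a non-significant interaction could be taken as evidence against a prognostic effect that is present. In the virus/Mycoplasma row the error runs the other way: the hypothesis is one of no effect, so a non-significant interaction, the likely result, would seem to support it even if virus status strongly predicted cure. Nor would a significant interaction support any of the three hypotheses as worded.

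**Working it through.** **Inputs from the article.** 135 per arm, 270 in total; reference failure about 5%; margin 7.5 points; one-sided alpha 0.025 and power 0.80 (Abstract and Sample size); alpha 0.05 for other tests (Analysis), taken as two-sided. The CRP subgroup row gives no cut-point. The 75th percentile in the planned sensitivity analysis gives 25% high, and 50% is run as an alternative.

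**Assumed.** Failure rates by subgroup, since the article gives none: 3% in the low group and 9% or 12% in the high group, equal in both arms, with the factor measured in every child.

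**The plan's own figure.** n per arm = (1.960 + 0.842)² × 2 × 0.05 × 0.95 / 0.075² = 7.85 × 0.095 / 0.005625 ≈ 133, close to the stated 135. Expected failures at 5%: 270 × 0.05 = 13.5.

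**What each test estimates (25% high, 12% versus 3%).**

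- Factor odds ratio in each arm: (0.12/0.88) / (0.03/0.97) = 4.41; log 1.484.
- Interaction: log 4.41 − log 4.41 = 0. It stays 0 whatever the factor odds ratio.

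**Hand check of main-effect power.** Pooled over arms there are 68 high and 202 low children. Expected failures are 68 × 0.12 = 8.16 and 202 × 0.03 = 6.06.

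- Variance of the log odds ratio: 1/8.16 + 1/59.84 + 1/6.06 + 1/195.94 = 0.309; SE 0.556.
- z = 1.484 / 0.556 = 2.67; power ≈ Φ(2.67 − 1.96) = 0.76.
- The interaction has SE 2 × 0.556 = 1.11 around a true value of 0.

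**Simulation.** 20,000 trials per scenario, two-sided 0.05. The main effect is tested by likelihood ratio, adjusted for treatment. For the Wald test, an empty cell counts as no rejection.

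| High group | Failure, low v high | Main effect | Interaction, LR | Interaction, Wald |
|---|---|---|---|---|
| 25% | 3% v 9% | 49% | 8.0% | 1.2% |
| 25% | 3% v 12% | 74% | 7.8% | 1.9% |
| 50% | 3% v 9% | 58% | 7.5% | 0.9% |
| 50% | 3% v 12% | 84% | 7.4% | 0.9% |

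With no factor effect at all (5% v 5%), the interaction test rejects in about 8% (LR) and 0.6-1.6% (Wald). The rates in the table are therefore essentially null rates. LR lies above 5% and Wald well below it because the arm-by-subgroup failure cells are sparse. Raising the contrast to 3% v 20% leaves the interaction rates at about 7-8% and 0.6-2.2%, while main-effect power reaches 98.6-99.8%.

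**The case against.** **The interaction test is the right analysis for the declared subgroup aim.** This stands. A reader might infer that the plan chose the wrong subgroup analysis. The Subgroup objective and the secondary research question in the Background both ask about effect modification, and the interaction term answers that. What fails is the match with the hypothesis column.

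**The prognostic question may be covered elsewhere.** This stands in part. The Analysis section says that binary outcomes will be analysed by logistic regression, which could cover the last secondary outcome. That outcome might even be meant as effect modification, since its covariates largely repeat those of the Background question. The stratified sensitivity analyses would also show cure by factor level. So the documents do not support saying that the question has no possible analysis, only that Table 1 names none for it. An article may leave model terms to the full plan, but here it fixes a specific test beside a specific hypothesis and the two do not match.

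**The interaction model also contains a subgroup coefficient.** True. A reader might infer that a real prognostic effect would almost never be seen. That describes the interaction test only. If the subgroup coefficient were read, it would reach significance in about 18-59% (Wald) or 35-76% (LR) of trials for failure of 3% v 10% to 3% v 15%. It is, however, the effect in one arm only, and the article does not name it as the test. Nor does the article say that the interaction p value alone will decide these hypotheses; all analyses are to report an estimate and a 95% CI.

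**The magnitude rests on assumptions.** This stands. That an interaction test rejects near its null rate when there is no interaction is true by construction. The 50% split with 3% v 12% implies 0.5 × 3% + 0.5 × 12% = 7.5% overall failure, above the planned 5%. Holding 5% overall with an odds ratio of 4 gives 65-67% main-effect power. Saliva is optional and requested only where serum CRP was not measured (Other testing), so full CRP data will not be available.

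**Conclusion.** The mismatch holds for all three subgroup rows. Each hypothesis is worded as an effect of the factor on cure, or as no such effect, and the assigned test addresses a different question. With the factor acting equally in both arms, the interaction rejects in about 7-8% (LR) or 1-2% (Wald) of trials, while a pooled main-effect test has about 49-84% power. Those power figures assume failure of 3% v 9-12% and a factor known for all 270 children; for CRP they are upper bounds. The interaction rates do not depend materially on the size of the assumed factor effect.

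The consequence is limited. The article calls these tests exploratory and unadjusted, few failures are expected, and the primary non-inferiority comparison, the sample size and the conduct of the trial are untouched. It is a minor correction to Table 1.

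**What to change.** 1. Keep the interaction term for the three subgroup analyses. Restate each hypothesis as an expected difference, or no expected difference, in the 5-day versus 10-day effect on cure between the subgroups.
2. Add a row for the prognostic question, covering the prognostic hypotheses now in the subgroup rows, the last secondary outcome and the third tertiary objective. Use logistic regression of clinical cure on treatment plus one baseline factor (age group, salivary CRP, high-level pneumococcal colonization, Mycoplasma, virus) with no interaction term. Report the factor's effect with its 95% CI over both arms and the number of children with the factor measured.
3. Move the age-group predictions about CRP, colonization and Mycoplasma out of the clinical-cure row, to sit with the tertiary objective on differences by age.

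The cost is some rewording of Table 1 and a few extra models on data already collected. No participants, visits or specimens are added.

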#### Secondary

The secondary objectives relate to the secondary outcomes and include assessment of whether the 5-day course is: (1) non-inferior to the 10-day course with respect to either participant or caregiver absenteeism (from daycare/school or work, respectively); (2) associated with lower rates of mild drug adverse reactions, anaphylaxis, or other severe drug adverse reactions than the 10-day course; (3) associated with superior adherence to study medications than the 10-day course; (4) non-inferior to the 10-day course with respect to recurrence of respiratory illness within 30 days of cure; and (5) associated with lower rates of antibiotic-resistant organism (ARO) colonization and/or disruption of the gut microbiome than the 10-day course.

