#### Follow up

The RA will phone the caregiver once at day 3–5 and once at day 7–10 to verify the clinical stability of the participant. Caregivers will also be explicitly informed that they can contact the study team in the event of a concern prior to the scheduled phone calls. The caregiver will be given a study diary to complete each day, which will include the following: temperature, dyspnoea (older participants), increased work of breathing, school attendance, caregiver absenteeism from work duties, days of mild diarrhoea, mild (abdominal discomfort, rash) and severe (anaphylaxis) drug adverse reactions, and the number of missed medication doses, if applicable. The caregivers will be instructed how to take their child’s temperature and assess increased work of breathing. Any participant who has persistent fever more than 3 days post-enrolment will receive an additional 5 days of open-label amoxicillin after the initial 5 days (i.e. will receive a guaranteed 10 days of antimicrobial agents). Any participant who worsens clinically subsequent to enrolment at any time point prior to the primary outcome visit will be urged to seek medical care without delay either at the site where recruitment took place or with another physician (e.g. family physician, walk-in clinic); all participants will be provided with printed documentation about the SAFER trial and contact information for the local Principal Investigator (PI) for the benefit of the medical professional re-evaluating the participant. The criteria for permanent discontinuation of the experimental aspect of the study protocol in an individual subject are as follows: failure to defervesce by day 4 post-enrolment; requirement for hospitalization because of worsening respiratory illness; severe reaction potentially associated with amoxicillin, such as a generalized allergic reaction (urticarial rash, bronchospasm, angioedema, hypotension, etc.); requirement for prohibited concomitant medications; completion of treatment/intervention as defined by the protocol; or clinical reasons believed by the physician to be life-threatening.

The daily symptom diary will include prompts to aid caregivers to remember the three daily doses of study medication. The RAs will also encourage optimal adherence to medication administration at baseline and at each of the two scheduled follow-up phone communications.

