These analyses will be exploratory. The following sensitivity analyses are planned: (1) intention-to-treat analysis; (2) strict per-protocol analysis including only those participants who were adherent to their medications and whose radiographs were reported by a radiologist to demonstrate alveolar infiltrates; (3) per-protocol analysis stratified by whether the saliva CRP was greater than the 75th percentile; and (4) per-protocol analysis stratified by whether a virus, an atypical pathogen, or high-level *S. pneumoniae* colonization was found in the NPS. If evidence is found of effect modification or confounding related to the above parameters additional analyses will be undertaken. The results of all analyses will be reported as estimate of effect, corresponding 95% CI and associated *p* values. All *p* values will be reported to three decimal places with those less than 0.001 reported as *p* < 0.001. The criterion for statistical significance will be set at alpha = 0.05. Table 1 provides a summary of the outcomes, corresponding hypotheses, measure, and method of analysis.

**Table 1 Tab1:** Variables, measures, and methods of analysis

Variable/outcome	Hypothesis	Outcome measure	Methods of analysis
Primary			
Clinical cure (per-protocol)	Short-course (5-day) treatment with high-dose amoxicillin is non-inferior to long-course (10-day) treatment	At visit (day 14–21) composite of: 1. Defervesced on or before day 4 2. No more than 1 further fever spike until visit 3. No tachypnoea and decreased work of breathing 4. No additional antibacterials given Dichotomous	Logistic regression
Secondary, between-group comparisons			
Absenteeism (caregiver, from work)	Short-course treatment is non-inferior to long-course treatment	Daily symptom diaries: self-reported number of caregiver-days absent from work (count)	Poisson regression
Absenteeism (child, from daycare/school)	Short-course treatment is non-inferior to long-course treatment	Daily symptom diaries: reported number of child-days absent from daycare/school (count)	Poisson regression
Mild drug adverse reactions	Fewer in short-course arm than in long-course arm	Daily symptom diaries: Reported number of child-days with diarrhoea, rash, abdominal pain, yeast infection (count)	Poisson regression
Anaphylaxis and other severe drug adverse reactions	Fewer in short-course arm than in long-course arm^a^	Daily symptom diaries, SAE reports. Dichotomous	Descriptive statistics

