Intention-to-treat	Results will remain robust	Clinical cure	Logistic regression
Strict per-protocol (those with adherence >80% and radiologist-verified pneumonia)	Results will remain robust	Clinical cure	Logistic regression

*SAE* serious adverse event, *RA* Research Assistant, *ARO* antibiotic-resistant organism, *CRP* C-reactive protein

^a^Too few events expected to be able to observe differences in treatment arms

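### The per-protocol principal analysis is justified only for non-inferiority, and intention-to-treat is reserved for clinical cure, so the secondary superiority hypotheses have no stated all-randomised analysis

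*Protocol article*

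**What the plan says.** Three statements in the Protocol article bear on this point.

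- **Principal analysis.** The Analysis section states: "The principal analysis will be per- protocol, as is recommended for non-inferiority trials". The reason given is that intention-to-treat tends to shrink differences between arms and so could produce a false finding of non-inferiority. The same sentence draws the contrast: "in a superiority trial, ITT analysis functions to buttress a conclusion of superiority".
- **Scope of intention-to-treat.** The text says "The following sensitivity analyses are planned: (1) intention-to-treat analysis" and names no outcome. Table 1 supplies the limit. Its sensitivity block is headed "Sensitivity analyses – for primary outcome only", and the row reads "Intention-to-treat Results will remain robust Clinical cure Logistic regression".
- **Superiority hypotheses.** The Secondary objectives ask whether the short course is "associated with lower rates of mild drug adverse reactions, anaphylaxis, or other severe drug adverse reactions than the 10-day course". They also ask whether it gives better adherence, and less resistant colonisation or gut-microbiome disruption. Table 1 assigns Poisson regression to mild reactions, logistic regression to adherence and to new colonisation, and linear regression to the microbiome. Severe reactions carry a directional hypothesis but receive descriptive statistics only.

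In Table 1 the per-protocol label stands on the primary row alone, which begins "Clinical cure (per-protocol". No secondary row names an analysis set.

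**The concern.** The article gives one argument for its principal analysis set, and that argument is specific to non-inferiority. It does not carry over to a hypothesis that the short course is better. By the authors' own account, intention-to-treat is the supportive analysis for such a hypothesis. Yet the only set described as principal is per-protocol, and the only set that contains all randomised children is assigned to clinical cure.

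The outcomes concerned are the benefits that motivate the trial: fewer reactions, better adherence, less resistance and less microbiome disruption. A per-protocol set is formed by what happens after randomisation. If membership is related to the outcome and differs between arms, the comparison loses the protection of randomisation. With no all-randomised analysis beside it, a reader of the results could not judge how much that matters.

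**Working it through.** The plan gives no expected rate or difference for the four tested superiority outcomes, so there is no figure to reproduce. The check sets the statements side by side.

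**Step 1: sort the secondary between-group rows of Table 1 by type of hypothesis.**

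| Outcome | Hypothesis | Method | Set named in the row |
|---|---|---|---|
| Caregiver absenteeism | Non-inferiority | Poisson | None |
| Child absenteeism | Non-inferiority | Poisson | None |
| Recurrent respiratory illness | Non-inferiority | Logistic | None |
| Mild adverse reactions | Superiority | Poisson | None |
| Severe adverse reactions | Superiority in direction | Descriptive | None |
| Adherence | Superiority | Logistic | None |
| New resistant colonisation | Superiority | Logistic | None |
| Microbiome disruption | Superiority | Linear | None |

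The stated reason for per-protocol fits the first three rows. It does not fit the other five, of which four are tested.

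**Step 2: look for an all-randomised analysis of those rows.** The text lists intention-to-treat without an outcome. Table 1 then restricts it to the primary outcome, both in the block heading and in the row. Read together, they leave no all-randomised analysis for any superiority row.

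**Step 3: ask whether the size of the bias can be derived.** For one arm, let *m* be the mean in all randomised children, *s* the share excluded and *x* the mean among those excluded. Then

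- per-protocol mean = (*m* − *s*·*x*) / (1 − *s*)
- shift from the all-randomised mean = *s*·(*m* − *x*) / (1 − *s*)

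The between-arm difference (10-day minus 5-day) therefore moves by

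*s*₁₀(*m*₁₀ − *x*₁₀)/(1 − *s*₁₀) − *s*₅(*m*₅ − *x*₅)/(1 − *s*₅).

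The article gives none of *s*, *x* or *m* for either arm, and the sign is open. Suppose exclusions fell mainly in the 10-day arm, on children with more reaction days than average (*x* > *m*). The contrast would then shrink, against the short course. Suppose instead they fell on 10-day children who took less drug and so had a lower value than average (*x* < *m*). The contrast would then grow, in favour of the short course. With no exclusions, or with excluded children who resemble the rest, the shift is zero. Bias is possible, but its size and direction cannot be stated from this document.

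**The case against.** The strongest reply is that the article never says the secondary outcomes are analysed per-protocol. Only the clinical-cure row has that label, and the principal analysis can be read as the primary comparison alone. A condensed article may leave secondary and safety sets to the full protocol or the analysis plan. This part stands: extending per-protocol to the secondary outcomes is a reading and not a quotation. It does not remove the point, because Table 1 is not silent on intention-to-treat. It positively confines it to clinical cure.

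A reader might also infer three stronger things, which the documents do not support.

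- **That children who stop because of a reaction leave the analysis, so that severe-reaction events drop out of the count.** The Follow up section does list "severe reaction potentially associated with amoxicillin, such as a generalized allergic reaction" among the criteria for discontinuation. But that list governs the experimental treatment and not analysis membership. It also includes having completed treatment, so as an exclusion list it would remove every completer. Severe reactions are summarised descriptively, the Safety and adverse events section records all adverse events, and the monitoring board reviews serious ones by arm.
- **That the adherence comparison is cut short by excluding non-adherent children.** An adherence condition is stated only for the strict per-protocol sensitivity analysis, which concerns clinical cure. Adding it there suggests that the ordinary set does not require it.
- **That the benefit on reactions is understated by a particular percentage.** Any such figure would rest wholly on invented rates of reactions and of stopping.

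**Conclusion.** The point holds in a limited form. The article justifies its per-protocol principal analysis by an argument confined to non-inferiority, and it expressly limits intention-to-treat to clinical cure. As written, the superiority hypotheses on mild reactions, adherence, resistant colonisation and microbiome disruption have no stated analysis of all randomised children, contrary to the article's own remark on superiority.

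That these outcomes would be analysed per-protocol is the natural reading and an assumption of this point. That bias would follow is a possibility that depends on an undefined set, so no size or direction is claimed. The consequence is confined to secondary outcomes. It is worth correcting, because those outcomes carry the case for the shorter course.

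**What to change.** Amend the Analysis section and Table 1 as follows.

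1. State that the per-protocol principal analysis applies to the non-inferiority comparisons: clinical cure, both absenteeism outcomes and recurrence.
2. State that adherence, new resistant colonisation and microbiome disruption are analysed in all randomised children as allocated. Some families may decline enteric specimens. Those children lack data under any set, and that is a separate matter from exclusion for protocol conduct.
3. State that mild reactions, and the descriptive counts of severe reactions, are reported for all children who took study medication.
4. Make per-protocol the sensitivity analysis for the superiority outcomes, and change the heading of the sensitivity block to match.

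If the full protocol or analysis plan already says this, aligning Table 1 is enough. The cost is wording only. The article already plans to follow children who fail or receive other treatment, and to record all adverse events, so no new data collection or change of sample size is needed.
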